## Meals+ Intervention

### Theoretical framework

The intervention is framed by the Socio-Ecological Model (SEM), which highlights the interaction between individuals and community or societal influences, explaining how behavior (i.e. diet) can be affected by multiple levels, including interpersonal influences as well as the home and neighborhood environment and social determinants of health [32]. At the individual level, we have the older adult, with specific personal factors related to nutrition and health-related constraints that can contribute to dietary outcomes, which includes, for example, physical limitations to accessing food and services in the community. Meals+ intervention components that address individual level dietary influences include healthy eating guidance by CHW, as well as recipes and nutrition information provided in the food bags to enhance individual-level knowledge and skills.

At the interpersonal level, CHW and meal-delivery staff can offer social support, resulting in decreased loneliness. CHW can also assist in providing health education and managing health and social needs through connection and coordination of resources at different levels of the SEM, such as food assistance benefits (policy level) and community food resources (community level). Home-delivered meals and food bags reduce barriers to accessing food in community settings. The next level, the organizational level, includes institutions that coordinate and ensure the execution of HDMP. Finally, the policy level includes public policies and programs that finance and sustain HDMP and other food assistance programs influencing the quality of life and ensuring food security for older adults.

The Social Cognitive Theory (SCT) also informs the Meals+ intervention. SCT is an interpersonal level theory that emphasizes a dynamic interaction between people (personal factors), their behavior, and their environments. The CHW interaction generates an important element to develop behavioral capability, and self-efficacy of participants using phone calls to set goals and create action plans to address nutrition, social or health-related issues. Sequential CHW calls provide reinforcement about issues related to the action plan, promoting an iterative process to keep participants on track with their goals and stimulate self-regulation. The food bags provide access to healthy foods, modifying the home food environment and offering recipes and tip sheets. Both experimental intervention elements contribute to improving knowledge about nutrition, attitudes about overall health, skills related to preparing food, and outcome expectations that eating better will result in improved health.

CHW calls combined with food bag delivery promote a supportive environment to help older adults improve their diet quality and related conditions. Intervention components facilitate improvements in social support and access to healthy food and community services, which can lead to improvements in diet quality. Fig. 2 shows the intervention logic model that explains the interaction between the intervention and expected outcomes. Household size, health literacy level, age, education level and use of assistance resources (e.g. Supplemental Nutrition Assistance Program - SNAP; Senior Produce Boxes; Housing Assistance) are potential moderators related to improvements in diet quality and other outcomes.

**Fig. 2 Fig2:**
[figure not shown]
Intervention Logic Model

### Intervention components– traditional meal delivery

MOWRI provides clients with a prepared meal, delivered to their homes Monday through Friday by a MOWRI driver who also conducts an informal well-being check with a brief social visit. Depending on the area, some clients receive a one-time delivery of five frozen meals. A professional, third-party caterer prepares meals to meet one-third of an older adult’s daily dietary requirements [33]; culturally and medically tailored meals are also available. (Fig. 1).

### Enhanced intervention components

#### CHWs

The first component of the Meals+ intervention is support from a certified CHW. The approach for CHW interactions with clients is to assess needs, identify gaps in care and resources, and then help the client through health coaching and resource coordination. Through these interactions, the CHW addresses social determinants of health, improving food and nutrition security through instrumental and social support, and increasing socialization by offering human connection. The coaching is conducted during four calls, which includes a brief form of motivational interviewing (MI), goal setting, and an action plan focused on addressing some of the client’s nutrition, health, or social issues (Fig. 1). At the final call (Week 12), CHW checks in with the client, and makes referrals to the health insurer or other appropriate community resources for any on-going or unmet needs. Then they conduct follow-up measures (diet quality, food and nutrition security, loneliness, and HRQOL) and ask about satisfaction with the intervention. Fig. 1 describes the content of each call. For any of the four coaching calls, if participants are unresponsive to multiple contact attempts from the CHW, that particular call is considered missed. The participants are contacted during the scheduled time for their next call.

####  Healthy grocery bags

Participants in the enhanced group receive a bag of healthy food once a month for three months. Foods may include, depending on availability, items such as cereal, rice, beans, peanut butter, milk, juice, oats, canned, frozen or fresh fruit, canned, frozen or fresh vegetables, canned poultry, frozen soups, frozen chicken, frozen fish, frozen ground beef. At least two items in each bag will be fruits and vegetables. Foods are provided through the regional food bank, food pantry network, and/or purchased with a discount at a retail store. While the bags are consistent in cost (approximately $75 per bag), the food content of the bags is not the same every month; thus, the bags may vary in terms of calories, macronutrients, or micronutrients. The study team documents and reports each bags’ food and nutrient content. Bags also include recipes and healthy eating guidance materials from different sources such as the SNAP-Ed program, MyPlate [34], the Nutrition and Aging Resource Center [35], and Community Nutrition Education at the University of Rhode Island (URI) [36].

#### Usual care condition

In this study arm, MOWRI provides participants with the traditional HDMP intervention described above that includes five days of prepared meals. After 12 weeks, participants in this group respond to the follow-up assessment and then are provided with one CHW support call as a delayed intervention. This call addresses questions about difficulties finding and accessing community resources and services that participants might need and gives referrals to resources as necessary, including support for filling out applications to internal or external services if needed. Participants in this group are then provided with one grocery bag as part of their next meal delivery.

### Outcomes and measures

#### Primary outcome

The primary outcome of the study is diet quality assessed by the Dietary Screening Tool (DST), which consists of 25 questions focused on dietary intake [37, 38] The DST score ranges from 0 to 100, with an additional 5 points for an affirmative answer regarding the consumption of dietary supplements or vitamins. The questions are based on the consumption frequency of different food groups (e.g. “How often do you usually eat fruit as a snack?”). Scores are treated as continuous variables, and participants are also classified into three groups based on their scores: < 60 “at risk”, 60–75 “possibly at risk”, and > 75 “not at risk”. The DST has been validated for older adults and has adequate sensitivity, specificity, and positive predictive values when compared with the Healthy Eating Index [39, 40].

#### Secondary outcomes

Secondary outcomes include food security, nutrition security, loneliness, and HRQOL. Food security is measured by the United States Department of Agriculture (USDA) 6-item Household Food Security Scale [41]. The scores represent the number of affirmative responses (0–6) with individuals classified in 3 different categories: 0–1 indicates food security, 2–4 indicates low food security, and 5–6 indicates very low food security.

Nutrition security is measured by a 2-item Nutrition Security Screener (NSS) developed by Tufts University, Kaiser Permanente, and Los Angeles Department of Public Health [42]. The NSS includes a short preamble to help with the definition of healthy foods for the respondent, listing examples of foods that support health and well-being. The first question is: “Thinking about the last 3 months, how hard was it for you or your household to regularly get and eat healthy foods?”. The “somewhat hard” respondents are classified as “low nutrition security”, and the “hard” or “very hard” responses are classified as “very low nutrition security.” The “not very hard” or “not hard at all” are classified as “high nutrition security.” The second part of the survey is composed of 13 questions related to the barriers faced by individuals to access healthy foods and are analyzed through binary responses (e.g. “The price of healthy foods limits your ability to eat healthier meals” and “Not having information about which foods are healthy limits your ability to eat healthier meals”).

Subjective isolation or loneliness is measured by the validated University of California, Los Angeles (UCLA) 3-Item Loneliness Scale [43]. The three questions are related to the three dimensions of loneliness (relational connectedness, social connectedness, and self-perceived isolation), with the following content: “How often do you feel that you lack companionship?”; “How often do you feel left out?”; and “How often do you feel isolated from others?”. The score classifies individuals into two different groups: “not lonely” (scores 3 to 5) and “lonely” (scores 6 to 9). The scores of each question are added to generate an individual score.

Health-related quality of life is measured by the Centers for Disease Control and Prevention 4-question measure. The questions explore self-reported general health status (e.g. “Would you say that in general your health is…”) and calculate the number of unhealthy days during the month. The estimation is calculated based on the number of unhealthy physical and mental days. Considering the unhealthy days measure, the participants will be classified into two different groups: “less than 14 days” or “greater than or equal to 14 days” [44].

### Evaluation activities

After the 12-week intervention period, participants in both arms are contacted by CHWs for the follow-up outcome assessment. Participants in the Meals+ arm are asked these questions after the Call 4 intervention component has been completed, while participants in the usual care arm are asked these questions before they receive the delayed intervention call content. For both study arms, the CHW asks about satisfaction with the home-delivered meals and the overall study. For the enhanced study arm, the CHW also asks participants about how much food they consumed from the food bags, use of recipes and educational materials, and satisfaction with the intervention. Participants in both arms receive an additional $30 incentive after completing the 12-week follow-up assessment.

Participants in the Meals+ arm are also asked if they might be interested in participating in a post-intervention satisfaction interview. Of the participants who consent, a subset is selected for interviews, aiming to include participants from all CHWs. UConn staff asks MOWRI for the contact information of those selected participants. Post-intervention interviews ask what participants think about the food bags, recipes, communication with CHW, perspectives about changes related to participation in the intervention (including diet, quality of life and eating habits), and strengths and limitations of the intervention. The participants that complete these interviews receive an additional $25 incentive. These interviews are audio-recorded, and the recordings are sent to a professional transcription company to be transcribed.

The Practical, Robust Implementation and Sustainability Model (PRISM) is the evidence-based framework for evaluation activities [45]. We are measuring PRISM domains using key informant interviews with MOWRI leadership and staff, CHWs and external partners; CHW notes from participant calls; participant evaluation surveys; process evaluation data; MOWRI report data; quality control checks of audiotaped CHW calls; nutritional analysis of food bags; cost tracking; and minutes of project meetings.

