Randomization is 1:1, with stratification of participants on living alone vs. living with others. Randomization is performed at the household level and in the case of more than one enrolled client per household, they are randomized to the same study arm. The Research Electronic Data Capture (REDCap) system randomly assigns participants within strata to one of the two conditions after the client completes the baseline survey. The assignment arm is not blinded for study team staff or participants. After randomization, the CHW tells the participant which group they were randomized to and describes the appropriate study arm processes. For participants in the Meals+ intervention group, the CHW describes the upcoming 12-week intervention and asks them to schedule a time for the first CHW coaching session within the next week. For participants in the usual care group, the CHW informs the participant that they will receive the usual MOWRI home-delivered meal service and that they will contact them in about 11 weeks to schedule a time for the 12-week call.

All plans for the design of the intervention and the evaluation were made using a CBPR approach, with decisions made jointly by University of Connecticut researchers and MOWRI leadership and staff, and additional input from community partner stakeholders. The academic-community team met at least weekly to discuss all project-related plans during the development of the intervention and to jointly solve implementation issues that arose during the pilot intervention phase.

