## Discussion

Home-delivered meal programs help to reduce nutritional risk and promote socialization among older adults. However, evidence shows that older adults still face challenges to address nutritional, social, and health needs [8–11, 19]. This pragmatic randomized controlled trial will examine the efficacy of an enhanced HDMP that includes CHW coaching and healthy grocery bag delivery on improving diet quality, food and nutrition security, loneliness and HRQOL in older adults. By comparing the outcomes of participants receiving enhanced services with those receiving usual services, the study will provide evidence on the additional benefits of incorporating innovative elements into the traditional HDMP.

The study has a rigorous randomized design. This ensures that the differences observed between the groups after the intervention are attributable to the intervention and not to other factors. The study is based on the CBPR approach, with the active contribution of MOWRI and community stakeholders in intervention development and implementation. Conducting the intervention in real world setting of MOWRI increases external validity, increasing the likelihood that the intervention enhancements can be generalized to other HDMP. The innovative additions of healthy grocery bags and CHW coaching will be important in the light of new opportunities for Medicaid reimbursement for services, including providing groceries for people with diet-related conditions or food insecurity and the “Food is Medicine” expansion [55].

This trial has some potential limitations. First, we will not have the ability to assess separate effects of each component of this multi-component intervention. However, interventions with multiple components can maximize the impact of the intervention on the target population, which might not be possible with just one component alone. Furthermore, the combination of components mimics the normal public health scenario, which works with several variables to address health problems [56, 57]. Beyond that, with our evaluation process, we could assess satisfaction with each intervention component and examine the relationship between intervention component delivery and outcomes.

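### At week 12 the self-reported outcomes are asked after Call 4 content in Meals+ but before any delayed CHW content in usual care, an avoidable arm-specific risk of reporting bias

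*Protocol article*

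**What the plan says.** Three sections of the protocol article agree on the week-12 sequence.

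- **Meals+.** Evaluation activities: "Participants in the Meals+ arm are asked these questions after the Call 4 intervention component has been completed". The CHWs section gives the same order. The final call opens with a check-in and referrals for unmet needs, and after that: "Then they conduct follow-up measures (diet quality, food and nutrition security, loneliness, and HRQOL) and ask about satisfaction with the intervention".
- **Usual care.** Evaluation activities: "participants in the usual care arm are asked these questions before they receive the delayed intervention call content". Usual care condition: "participants in this group respond to the follow-up assessment and then are provided with one CHW support call".
- **Who asks.** "participants in both arms are contacted by CHWs for the follow-up outcome assessment" (Evaluation activities).
- **Blinding.** "The assignment arm is not blinded for study team staff or participants" (Enrollment and randomization process).

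The DST is scored from self-reported frequency of eating food groups (Primary outcome). The baseline interview is done before randomization, so it is the same in both arms. The Discussion says of the randomized design: "This ensures that the differences observed between the groups after the intervention are attributable to the intervention and not to other factors". The limitations that follow do not mention the order of the week-12 interview.

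**The concern.** Randomization makes the groups comparable at entry. It does not make the measurement comparable if the outcome is collected by a different procedure in each arm. Here one arm answers after a supportive conversation with a CHW and the other answers without one. In an unblinded trial with self-reported outcomes, that conversation may affect what is reported through mood, social desirability or priming.

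The order is tied to assignment, so it cannot be separated from treatment. It differs only at follow-up, so any shift it causes enters the follow-up contrast directly. The target difference on the DST is small (2.0 points against a standard deviation of 12.0), which leaves little room for a measurement artefact.

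**Working it through.** **1. Is the order really different by arm?** In Meals+, two sections (CHWs, Evaluation activities) put the Call 4 content first and the outcomes second. In usual care, two sections (Usual care condition, Evaluation activities) put the outcomes first and the CHW content second. There is no conflicting statement.

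**2. Can the planned analysis remove it?** Take a reporting shift averaging b across analysed Meals+ participants at follow-up, and zero elsewhere.
- In the model under Data analysis, the baseline values carry no trace of b, and b is carried by the arm-by-follow-up term. The estimated difference is the true difference plus b.
- Multiple imputation built on the observed follow-up values carries b forward.
- A larger sample shrinks the standard error but not b.

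**3. Reproduce the design figures** (Sample size and power calculations: SD 12.0, difference 2.0, 574 per arm, alpha 0.05).
- SE = 12 × √(2/574) = 0.708 points.
- Power, two-sided normal approximation: 2.0/0.708 = 2.82; Φ(2.82 − 1.96) = 80.6%, as stated. A one-sided test would give 88.1%, so a two-sided test is what the plan used.
- Enrolment: 2 × 574 = 1,148; 1,148/0.70 = 1,640, as stated.
- Smallest significant difference: 1.96 × 0.708 = 1.39 points.

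**4. Illustrate the sensitivity.** With no true effect and an average shift b in Meals+, the rejection rate is [1 − Φ(1.96 − b/SE)] + Φ(−1.96 − b/SE). The values of b are assumptions; the documents give none.

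| Assumed b (DST points) | b in SD units | Share of 2.0-point target | Rejection rate |
|---|---|---|---|
| 0 | 0 | 0% | 5% |
| 0.25 | 0.02 | 12.5% | 6.4% |
| 0.5 | 0.04 | 25% | 10.9% |
| 1.0 | 0.08 | 50% | 29.2% |

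Only the part of a shift caused by the position of Call 4 belongs in this table. Shifts due to lack of blinding or to the earlier coaching calls are separate.

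**5. Effect or reporting?** The answer differs by outcome.
- *DST:* it asks about usual consumption. A call just before the interview cannot plausibly change that, so a difference due to order would be a reporting effect.
- *Nutrition security (first question) and unhealthy days:* these refer to the last three months and the month, so the same reasoning applies.
- *Loneliness and self-rated general health:* the items as quoted carry no recall window. An immediate benefit of the call and a change in reporting cannot be told apart.

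**The case against.** The best case for the plan has several parts.

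- **Assessing usual care before its delayed content is right.** This stands, because the reverse would contaminate the control arm. The avoidable part is the late position in Meals+.
- **Assessing after Call 4 captures the full intervention.** This has some force for loneliness, since more social contact is an intended effect of the CHW component. It has little force for usual dietary intake.
- **An unblinded pragmatic trial carries reporting bias anyway.** This is true. Meals+ participants have had earlier coaching calls and know their arm, and reordering leaves that in place. It removes only the order component, at almost no cost.
- **Not every Meals+ participant receives Call 4 content.** Calls can be missed, and people who stop home-delivered meals lose the CHW calls but may still be followed up. The shift averaged over the arm would then be smaller than the shift per person.

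A reader might also infer more than the documents support. They do not show that the shift favours Meals+: talking about unmet needs just beforehand could also increase reported hardship. They do not describe Call 4 as diet coaching; the text gives a check-in and referrals, and the call content is in a figure not available here. They do not say that the interview follows within minutes, and after the pilot a call event may span several calls. Nor do they say that the CHW who coached a participant is the one who interviews that participant. Finally, usual-care participants have already spoken with a CHW for consent, baseline and allocation, so what they lack at the interview is coaching content, not all CHW contact.

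**Conclusion.** The concern holds as a risk of bias. The order of the week-12 interview differs by arm, this is stated consistently, and none of the planned adjustment, imputation or sample size can undo its consequences. Size and direction are unknown.

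The error rates of 6.4%, 10.9% and 29% rest on the assumed shifts, a true null, a two-sided 5% test and the plan's own SD and analysed sample. They show how sensitive the design is to a small artefact; they are not estimates for this trial. It would be too strong to say that a bias towards Meals+ is built into the primary outcome.

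For the DST, an order effect would be a reporting artefact. For loneliness and self-rated health it would be an inseparable mix of reporting and immediate effect. The Discussion's statement that between-group differences come from the intervention alone is stronger than this measurement procedure allows. This should be fixed, since the remedy is cheap, but it does not invalidate the trial.

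**What to change.** 1. From now on, ask the outcome block first in both arms at week 12, in the same script order, before any Call 4 content (Meals+) or delayed-call content (usual care).
2. Record for each participant which order was used, and record the date of the switch. Report both descriptively. A comparison of results before and after the switch would compare calendar periods, not randomized orders, so it should not be read as a test of the order effect.
3. Add to the limitations that the outcomes are self-reported, collected by CHWs and unblinded, and that participants assessed before the switch had the arm-dependent order.
4. Soften the Discussion sentence so that it claims comparability at randomization and does not rule out every other explanation.

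**Cost.** A reordered call script, a short CHW refresher and, where required, submission of the change to the IRB. The figures of 574 per arm, 80.6% power and 1,640 enrolled stay as they are. There are two downsides: Call 4 falls outside the measured dose, and participants already assessed keep the old order.
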